## Abstract

**Background:**

Falls are the leading cause of fatal and non-fatal injuries among older adults. Older emergency department (ED) patients who present for evaluations after falls have a 30% higher risk of falling again in the subsequent 6 months than age-matched controls. Although EDs frequently evaluate older adults after their falls, the typical evaluation consists of an injury assessment alone. As such, an opportunity is lost to assess and address the potential causes of falls in this vulnerable population. In this manuscript, we present a multidisciplinary fall prevention protocol for a pilot study of older adult ED patients who recently sustained a fall (GAPcare: the Geriatric Acute and Post-acute Fall Prevention Intervention).

**Methods:**

GAPcare is a randomized single-blinded pilot study. Participants in GAPcare are 120 older adults (≥ 65 years old) who present to 1 of 2 academic US EDs after a fall. We randomly assign participants 1:1 to an intervention or a usual care (control) arm. In the intervention arm, the patient’s ED physician, a pharmacist, and a physical therapist (PT) collaborate to identify and address any risk factors that may have contributed to the fall. Intervention arm participants and their caregivers return home with a medication-related action plan to taper or stop potentially inappropriate medications and to address polypharmacy and a PT assessment and plan. Participants in the usual care arm receive standard assessments and care in the ED and a home safety brochure. Participants in both study arms complete fall calendars for 6 months to document the number of falls and healthcare visits during follow-up. The primary outcome is feasibility of the GAPcare fall prevention intervention (number and proportion of screened participants who are eligible, recruited, and retained; impact on ED length of stay), while the secondary outcome is to estimate its initial efficacy.

**Discussion:**

The GAPcare-ED fall prevention intervention has the potential to promote older adult-sensitive care for millions of Americans presenting to EDs after falls and establish a protocol for a future large-scale randomized controlled trial on this topic.

**Trial registration:**

ClinicalTrials.gov, NCT03360305. Trial registration date: December 4, 2017. Protocol version: 1

## Background

The Centers for Disease Control and Prevention estimate that by 2030, nearly one in five persons in the US will be ≥ 65 years old [1]. These older adults will comprise an increasing proportion of emergency department (ED) patients, and falls are the leading cause of fatal and non-fatal injuries that bring this population to the ED for evaluations [2]. ED evaluations for falls typically involve a focused assessment to rule out acute injuries, but do not identify modifiable risk factors to prevent subsequent falls [3–5]. ED patients rarely receive instructions to follow-up with clinicians that can address reasons for the fall [6]. Currently, only 3.7% of older adults receive fall guideline concordant care when they present to the ED after a fall [7]. According to the American Geriatrics Society and British Geriatrics Society guidelines, this care should include a multifactorial fall risk assessment that should be performed for all older persons who live at home and seek medical care in the ED because of a fall [8].

An interdisciplinary team of pharmacists and physical therapists (PTs) who perform standardized fall assessments is a key criterion for US geriatric ED accreditation [9]; however, currently, no applicable model exists to guide this care. Although falls are considered one of four high-yield research opportunities in geriatric emergency medicine [10], there is a notable lack of research in ED-based interventions to reduce the occurrence of recurrent falls among seniors. Preventing subsequent falls is critical to stop the cascade of functional decline, loss of independence, hospitalization, and death, which frequently follows a fall. Annual Medicare costs for adult falls are currently estimated to be $31.3 billion [11], and failure to find new, effective strategies to address falls in this population will lead to increased costs as the US population ages.

To address the lack of fall prevention research in the ED, we developed GAPcare (the Geriatric Acute and Post-acute Fall Prevention Intervention). This intervention brings together patients, caregivers, pharmacy and PT professionals, and clinicians to provide a patient-centric, collaborative approach to fall prevention that bridges the ED visit with outpatient resources. Performing a fall prevention intervention in the ED (as opposed to after the ED visit) provides more timely evaluation, which is of critical importance because seniors are at high risk of recurrent falls in the immediate post-fall period [12]. Unlike other current fall prevention protocols, this intervention starts immediately after the fall in the ED when patients and caregivers are highly engaged and motivated to prevent further fall occurrences [13]. The purpose of this manuscript is to describe the study protocol of the initial GAPcare investigation.

## Purpose and methods

The GAPcare study aims are to (1) examine the feasibility of the GAPcare intervention by assessing the number of participants who are eligible, recruited, and retained and measure the impact on ED length of stay (LOS); (2) determine if the GAPcare intervention (versus usual care) reduces subsequent falls and ED visits and hospital admissions in the 6-month follow-up; and (3) solicit feedback from participants on the utility and barriers of the GAPcare intervention and collect suggestions for improvement of the intervention. The rationale for completing this pilot trial prior to completing a definitive study powered for efficacy was to assess whether patients, caregivers, and clinicians were open to exploring prevention efforts with our pharmacists and PTs immediately after an injury, whether we could perform the intervention within the time constraints of a typical ED visit, and to obtain initial estimates of efficacy to help us determine the sample size for the subsequent definitive trial.

### Design of the GAPcare intervention and study protocol

This study is a two-site parallel group, single-blinded pilot randomized controlled trial (RCT). The hospital Institutional Review Board approved the study. We registered the trial at ClinicalTrials.gov (NCT03360305). The GAPcare intervention incorporates key elements of prior fall interventions [14–18]. The intervention was developed from these key elements and shaped by expert opinion from a team of geriatricians, health service researchers, geriatric-specialized PTs, and case managers, as well as an emergency medicine residency-trained pharmacist. This group of experts also comprise this pilot RCT’s research team and assisted in the creation of the study protocol.

### Setting

The study is being conducted at two main sites that belong to the same health system in Providence, Rhode Island: Rhode Island Hospital, an academic tertiary-care hospital, and The Miriam Hospital, an academic community hospital. The two participating study sites represent the ideal environment for this pilot study. Rhode Island Hospital is the only federally designated Level I Trauma Center in the state and has an annual ED census of 105,000. The Miriam Hospital provides care to a primarily community-dwelling geriatric population with a high injury and illness acuity and has an annual ED census of 73,000.

### Eligibility

Patients, their caregivers, and ED clinicians are recruited jointly to participate in the study. Study eligible patients are 65 years old or older, English-speaking, able to provide written informed consent (or have a legally authorized representative consent), and present to the ED after a fall. Participants must be community-dwelling or live in assisted or independent living communities. The treating clinician must intend to discharge the patient after their initial evaluation. Patients are excluded if their mental status is altered (i.e., intoxicated, agitated), they plan to leave the state in the ensuing 6 months (which limits retention for follow-up and engagement in treatment plans), are undomiciled, or cannot be reached by telephone.

### Recruitment and enrollment

Research staff review the ED Electronic Health Record (EHR) (Epic®) for ED patients presenting after a fall. Participants are recruited when PT and pharmacy specialists are available, Monday through Friday from 7 AM to 4 PM. The patient’s ED clinician is asked to confirm that he/she plans to discharge the patient home. If this outcome is likely, the research staff confirms eligibility with the patient, invites the patient to enroll, and asks them to provide written consent for participation. Caregivers and treating clinicians are also asked to consent to study participation.

We first assess each patient’s decisional capacity. For patients who score less than 4 on the Six-Item Screener [19] (a screen for cognitive impairment) but are interested in participating in the study, the legally authorized representative is asked to provide written consent.

After consent, each participant is randomized 1:1 to the intervention arm or usual care. Randomization is performed using REDcap and is based on randomization tables that stratify patients by study site. Enrollment staff do not have access to the allocation scheme before enrolling participants. It is not possible to blind the participants and treating clinicians to the allocation arm as they would be able to identify pharmacists and PTs at the bedside. However, the staff member who performs the assessment at 6-month follow-up is blinded to allocation arm.

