### Sample size

This early stage investigation is designed to provide a preliminary indication of the proportion of screened participants who are eligible, recruited, and retained, with the goal of estimating these proportions with a standard error of less than 5%. Assuming the maximum possible variability for each of these proportions, the sample size of 120 produces a standard error of 4.6%, enabling estimation of a margin of error of ± 8.9%. A second feasibility aim was estimating if there was a major difference in ED LOS between groups. For *α* = 0.05 with a two-sided test and assuming a standard deviation of 120 min, a sample size of 52 per group has adequate power (*β* = 0.83) to detect a difference of 65 min. or more. To allow for non-parametric tests which may be necessary given the skewed nature of ED visits, a 15% increase in sample size or 60 per group will yield the same power [27].

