### Data analysis

#### Feasibility

We collect the following feasibility measures and will report them descriptively [28]: number of patients screened, proportion eligible, number of patients recruited, time required to recruit, number of patients unable to provide consent, number of patient refusals, number of dropouts, and retention at each follow-up time point. We will use frequencies, proportions, rates, means/medians, and standard deviations and other measures of variability, as appropriate, to report on these feasibility measures. Also, we keep a record of lessons learned during the implementation of this study. To compare the median ED LOS between participants in both study arms, we will use the Wilcoxon-Mann-Whitney test and bootstrapping to generate a 95% confidence interval for the median difference in ED LOS. We will also examine the length of time required to complete the pharmacy and PT consultation in the intervention arm to determine if the intervention is feasible within the timeframe of an ED visit.

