#### Initial efficacy

We will complete the analyses on an intention-to-treat basis; participant outcomes will be analyzed according to their allocated arm, irrespective of the intervention received. Therefore, patients who are admitted or discharged to a skilled nursing facility after randomization will be included in the analysis.

We will compare the proportion and median/mean number of recurrent falls, ED visits, and hospital admissions over 6 months occurring in each arm using Fisher’s exact test (proportions) and Wilcoxon’s and Student’s *t* test (occurrence). If sample size permits, we will conduct a survival analysis for a time-to-event analysis. Survival time will be defined as the time from randomization to the time of the first recurrent fall. Dates and times for this outcome will be obtained from the fall calendar and EHR review. For this analysis, we will first use the Kaplan-Meier method to estimate time to the recurrent fall. Next, we will use the log-rank test to test differences between survival curves for the intervention vs. usual care arm. Finally, hazard ratios and 95% confidence intervals will be calculated using the Cox proportional hazards model; additional analyses will adjust for baseline differences in physical function. We may also use multivariate frailty models, which are an extension of traditional survival analyses that allow for multiple failures (in this case falls) and include random effects that take into account underlying individual predisposition to falling.

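### Randomisation is stratified by site but the named between-arm analyses do not use site; for ED length of stay this gives up some power if the two EDs differ

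*Protocol article*

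**What the plan says.** Recruitment and enrollment: "each participant is randomized 1:1 to the intervention arm or usual care", and the allocation "is based on randomization tables that stratify patients by study site". No block scheme is described.

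Setting: the two EDs differ in type and volume. "Rhode Island Hospital is the only federally designated Level I Trauma Center in the state and has an annual ED census of 105,000"; the second, a community hospital that is also academic, "has an annual ED census of 73,000". No LOS is given for either.

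Data analysis, Feasibility: "To compare the median ED LOS between participants in both study arms, we will use the Wilcoxon-Mann-Whitney test", with a bootstrap 95% confidence interval for the median difference. Site is not mentioned.

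Data analysis, Initial efficacy: Fisher's exact test for proportions, Wilcoxon and t tests for numbers of events, and, if numbers allow, Kaplan-Meier curves, for which "we will use the log-rank test to test differences between survival curves for the intervention vs. usual care arm", followed by Cox models. The one adjustment named is for physical function. The optional frailty models carry a random effect for the individual, not for site.

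**The concern.** A factor used to stratify the randomisation is normally carried into the analysis. If it predicts the outcome and is left out, the between-site variation stays in the noise against which the arms are compared. If allocation is also balanced within site, that variation has already been removed from the treatment comparison, so the unstratified standard error is larger than the true one and the test rejects too rarely.

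Conservatism is not the safe direction for LOS. LOS is a burden outcome: the question is whether a 20-minute pharmacy consultation and a 20-30-minute physical therapy consultation lengthen the visit. A test that rejects too rarely makes it easier to conclude that there is no impact. LOS is also the only between-arm comparison for which the Sample size section gives a power.

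**Working it through.** **Inputs from the protocol (Sample size).** Alpha is "0.05 with a two-sided test"; SD of LOS 120 min; difference 65 min; 52 per group, raised by 15% for a rank test (52 × 1.15 = 59.8, so 60). The protocol does not say whether 120 min is the total or the within-site SD.

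**Assumptions, not in the documents.** Gap D between site means of 0 to 120 min; equal site sizes (a 70/30 split was also tried); permuted blocks of 4 within site, or simple allocation.

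**The plan's own figure first.** Power = Φ(65 / (120·√(2/n)) − 1.96). At n = 52 this is 0.789 (0.781 by noncentral t), not the stated 0.83, which needs 58 or 59 per group. At n = 60 it is 0.843 (0.837 by t). That discrepancy is a separate matter; 0.843 is the reference below.

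**Normal approximation, total SD 120, n = 60 per arm, blocked.** Within-site SD: w = √(14400 − D²/4). The unstratified standard error is too large by the factor 120/w. Its type I error is 2Φ(−1.96·120/w).

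- Unstratified power = Φ((65/√(2/60) − 1.96·120)/w)
- Site-adjusted power = Φ(65/(w·√(2/60)) − 1.96)

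Example, D = 90: w = √(14400 − 2025) = 111.2; ratio 120/111.2 = 1.079; 65/√(2/60) = 356.0. Unstratified power is Φ((356.0 − 235.2)/111.2) = 0.861; adjusted power is Φ(356.0/111.2 − 1.96) = 0.893.

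| D (min) | SE ratio | Type I error, unstratified | Power, unstratified | Power, site-adjusted |
|---|---|---|---|---|
| 0 | 1.000 | 0.050 | 0.843 | 0.843 |
| 30 | 1.008 | 0.048 | 0.845 | 0.849 |
| 60 | 1.033 | 0.043 | 0.851 | 0.865 |
| 90 | 1.079 | 0.035 | 0.861 | 0.893 |
| 120 | 1.155 | 0.024 | 0.878 | 0.929 |

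If 120 min is instead the within-site SD, adjusted power stays at 0.843 and unstratified power is 0.828, 0.809 and 0.781 at D = 60, 90 and 120.

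**Simulation of the actual tests** (5,000-6,000 trials per cell, so a standard error of about √(0.85 × 0.15/5000) = 0.005 on each power). Power of Wilcoxon-Mann-Whitney vs van Elteren, equal sites:

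| D (min) | Blocked, normal | Blocked, lognormal | Simple allocation, normal |
|---|---|---|---|
| 30 | 0.818 vs 0.820 | 0.906 vs 0.910 | 0.819 vs 0.817 |
| 60 | 0.826 vs 0.842 | 0.901 vs 0.918 | 0.816 vs 0.833 |
| 90 | 0.831 vs 0.869 | 0.897 vs 0.936 | 0.812 vs 0.861 |
| 120 | 0.845 vs 0.908 | 0.883 vs 0.955 | 0.814 vs 0.910 |

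With blocking and normal data, the unstratified type I error was 0.037 at 90 min and 0.022 at 120 min, against about 0.05 for the stratified test. With a 70/30 split the losses were slightly smaller (0.820 vs 0.855 at 90 min; 0.834 vs 0.889 at 120 min). With simple allocation the unstratified type I error stayed at 0.048-0.054, but the power shortfall was larger: 4.9 points at 90 min and 9.6 at 120 min.

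**The case against.** **A condensed article may leave stratified versions of tests to the full plan.** Fair in general, and silence alone would not count. Here, though, the article names the test for each outcome and one adjustment covariate, and leaves out the only factor used in the randomisation.

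**The loss may be negligible.** This stands as a limit on size. Trauma designation and census are not LOS. Both hospitals are academic and in one health system. Enrolment is confined to patients expected to go home, on weekdays from 7 AM to 4 PM, which narrows case mix. Gaps of 90 and 120 min would mean that site explains 2025/14400 = 14% and 3600/14400 = 25% of LOS variance, and nothing in the documents shows that.

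**Conservatism needs balance within site.** Correct. Stratified tables do little without blocking, so blocking is likely, but the article does not state it. Without it only the loss of power remains.

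**Power does not fall below plan.** Correct if 120 min is the total SD: unstratified power is then 0.84-0.88 by the normal approximation, and the loss is a gain forgone. Nor is the false-positive rate inflated.

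**Two stronger readings are tempting and not supported.** A reader might infer that standard errors are too large in every between-arm analysis. Adjusting a Cox model for a prognostic factor does not generally shrink the standard error of the log hazard ratio, and Fisher's test has no such standard error; the Discussion also says that the study is not powered for recurrent falls. A reader might also infer that adjusting LOS for the time from arrival to randomisation would save many patients. The article neither defines when LOS starts and stops nor lists that interval among its data, and gives no basis for its share of the variance.

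**Conclusion.** The mismatch between design and analysis is real and matters chiefly for LOS. The direction is firm: if LOS differs between sites, the unstratified Wilcoxon-Mann-Whitney test is less powerful than its stratified form. The size is conditional on a gap that the documents do not give. Under blocked allocation the loss is at most about 2 points up to 60 min, 3-4 points at 90 min and 5-7 points at 120 min, a full SD. The test is then conservative at the larger gaps, so a true prolongation is easier to miss. If the sites do not differ, stratifying costs essentially nothing. For the efficacy analyses the reason to use site is consistency with the randomisation, not a demonstrated loss. This is a free improvement, not a flaw that invalidates the trial.

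**What to change.** In Data analysis, Feasibility: compare LOS with a site-stratified Wilcoxon (van Elteren) test and draw the bootstrap samples within site by arm. If allocation is not blocked within site, the estimate itself should also combine the within-site median differences, so that the interval matches the estimate.

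In Data analysis, Initial efficacy: stratify the log-rank and Cox analyses by site.

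The cost is a few words. Site is known for every participant, no new data are needed, and the sample size does not change. The change should be made before the arms are compared.

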### In-ED procedures

After initial evaluation by the ED treatment team, patient participants are asked questions from the baseline questionnaire and their current medications are recorded by the research staff using previously published best practices for medication reconciliation [20]. Intervention patients receive individually tailored pharmacy and PT consultations according to the GAPcare protocol (see Table 1). Intervention participants receive all components of the intervention arm unless they refuse. The research staff delivers the intervention while participants are awaiting results of laboratory testing and imaging (see Fig. 1). Usual care participants receive care as dictated by the ED treatment team alone and a brochure from the Centers for Disease Control and Prevention about home safety. The research staff completes a timed up and go test on all participants regardless of study arm. All participants are provided with a fall calendar that allows them to record any new falls and healthcare visits at the time they occur for the following 6 months. It is at the discretion of the ED treatment team to contact the primary care physician (PCP), consult a case manager, and provide medical equipment (e.g., walkers, canes). Both intervention and usual care participants, their caregivers, and clinicians are asked to complete an end-of-visit survey to record their satisfaction with the care delivery, perceived barriers and facilitators, and suggestions for improvement.

**Table 1 Tab1:** In-ED procedures for intervention patients

Personnel	Description	Administration
Pharmacist assessment and medication-related action plan		
Pharmacist	The pharmacist study protocol consists of the following steps: • Review the research staff obtained medication list [20]. • Perform motivational interviewing with the patient and/or caregiver to identify 1–3 medication recommendations, such as cessation or tapering of medication that increase fall risk. • Communicate the medication-related action plan (MRAP) in writing to the patient and ED treatment team. A facsimile copy of the MRAP is sent to the primary care provider (PCP) at the end of the visit via the newly created EHR structure.	• 20 min • In-person evaluation
Physical therapy assessment and action plan		
Physical therapist	The PT has the following responsibilities: • Performs a gait, balance, and lower extremity strength assessment. • Assesses the patient’s ability to function independently on discharge and assists with discharge planning. • Recommends outpatient services/referrals, such as referral to outpatient or home PT and occupational therapy, a home-safety evaluation, community fall prevention programs, or if necessary direct admission to a skilled nursing facility. • Communicates the PT action plan (PTAP) in writing and in person to the patient and ED treatment team. A facsimile copy of the PTAP is sent to the PCP at the conclusion of the visit via the newly created EHR structure.	• 20–30 min • In-person evaluation

*MRAP* medication-related action plan, *PCP* primary care provider, *PT* physical therapist, *PTAP* physical therapy action plan, *EHR* electronic health record

